## Abstract

**Background:**

There is growing evidence that health and social outcomes following motor vehicle crash injury are related to cognitive and emotional responses of the injured individual, as well as relationships between the injured individual and the compensation systems with which they interact. As most of this evidence comes from other states in Australia or overseas, investigation is therefore warranted to identify the key determinants of health and social outcomes following injury in the context of the New South Wales motor accident insurance scheme.

**Methods/Design:**

In this inception cohort study, 2400 participants, aged 17 years or more, injured in a motor vehicle crash in New South Wales will be identified though hospital emergency departments, general and physiotherapy practitioners, police records and a government insurance regulator database. Participants will be initially contacted through mail. Baseline interviews will be conducted by telephone within 28 days of the injury and participants will be followed up with interviews at 6, 12 and 24 months post-injury. Health insurance and pharmaceutical prescription data will also be collected.

**Discussion:**

The study results will report short and long term health and social outcomes in the study sample. Identification of factors associated with health and social outcomes following injury, including related compensation factors will provide evidence for improved service delivery, post-injury management, and inform policy development and reforms.

**Trial registration:**

Australia New Zealand Clinical trial registry identification number -
ACTRN12613000889752. Available at: ANZCTR Registered FISH Study.

## Background

Worldwide, road traffic injuries are ranked twelfth in terms of contribution to Disability Adjusted Life Years
[1]. Whilst 90% of the road traffic injury burden falls on low or middle income countries
[1,2], it also has major personal and societal implications in high income countries such as Australia
[3].

The economic loss associated with road traffic injuries in Australia is equivalent to nearly 3% of the national Gross Domestic Product. The 2009 report by The Australian Bureau of Infrastructure, Transport and Regional Economics estimated a total cost, in Australian Dollars (AUD), of $2.8 billion, associated with road traffic injuries in the nation’s most populous state of New South Wales (NSW)
[4]. Nearly 70% of this cost was associated with human factors such as disability, costs of medical services, lost productivity and insurance administration. Clearly, understanding factors associated with the human costs are a priority for reducing the socio-economic burden of injury arising from road traffic injuries
[4].

There is growing evidence that health and social outcomes following road traffic injuries are related to the cognitive and psychosocial responses of the injured person
[5], the interaction between the injured individual and the systems they experience following an injury
[6-8]. This is in addition to the specific physiological and anatomical effects of the injury. Studies have also suggested that pre-injury socio-demographic and health characteristics are associated with adverse functional and disability outcomes after injury, independent of the anatomical nature and severity of injury
[9,10].

Many studies have investigated recovery after road traffic injuries; however the focus of the research has generally been on particular types of injury such as orthopaedic injury or whiplash associated disorders
[11-13]. In a time series study, it has been shown that health outcomes of people with whiplash injury improved after legislative change. The changes included removal of financial compensation for "pain and suffering" for whiplash, introducing clinical practice guidelines for its treatment; and change in regulations to permit earlier acceptance of compensation claims, and earlier access to treatment
[14].

The ESPARR cohort from France reported that only 45% of the participants with mild-to-moderate injury in road traffic crash reported to have fully recovered from the injury
[15]. In Victoria, Australia, cohort studies following up orthopaedic and trauma patients have reported worse short term and long term health, vocational and functional outcomes, among people claiming compensation through Transport Accident Commission (TAC)
[11,16]. Similar findings have also been reported in context of work injuries, with injured people receiving compensation having worse health outcomes and a slower recovery than people with similar injuries not receiving compensation
[17,18]. In another study in Victoria, 8% of participants reported loss of earnings and a median of 33 days of work disability for injuries that did not require any hospital stay
[19].

As insurance and compensation systems vary by jurisdiction, and there has been little research identifying key factors related to recovery in NSW. The Motor Accident Authority in NSW, has identified several limitations in the current compulsory scheme, for example the scheme need to establish fault means the NSW CTP Scheme is essentially adversarial, delayed payments, high cost and disputes
[20]. Hence, further investigation is warranted to confirm the key determinants of health and social outcomes in a broader cohort of people following road traffic injury in NSW, and in particular to identify the specific features of the compensation process that might facilitate or impede recovery.

This study takes a broad view. It investigates the potential factors that may influence health and social recovery, including pre- injury socio-demographic and health characteristics, injury characteristics, utilisation of health services, and compensation factors such as claims process, treatment, liability and fault, and legal representation.

### Objectives

The specific objectives of the study in context of the New South Wales, compulsory third party scheme are as follows:

1. To determine whether particular prognostic factors, including those related to health, socio-demographic and economic status, are predictors of outcome following injury.

2. To determine whether particular factors linked to compensation are predictors of outcome.

## Methods/Design

### Settings

NSW is the most populous state of Australia with an estimated population of 7.29 million that is 34.5% of the population of Australia. Over 73% of the state’s population lives in cities. There were over 5,876,000 vehicles registered and 5,655,000 licensed drivers in NSW in 2013. Nearly 42,000 crashes are recorded every year with over half of the crashes leading to casualties
[10].

Compensation from the third party insurance scheme (also called Compulsory Third Party insurance or CTP), is available for persons killed or injured as a result of a motor vehicle crash. The scheme does not cover the at fault driver; although there are exceptions for people with very severe injuries (from 1 October 2007 for adults). It provides benefits for injured persons that include medical treatment, rehabilitation expenses, compensation for lost earnings, and for other accident-related expenses. The scheme is designed to support early treatment and recovery. In the 2011–2012 financial year, approximately 14,000 claims were made and payments to injured people were approximately $AUD 1,290 million
[21].

### Design

The study will utilise an inception cohort design. Recruitment will be conducted through metropolitan and rural hospital emergency departments, general practitioners, physiotherapy clinics, police crash records and the claims database of a government insurance regulator (the NSW Motor Accidents Authority). Minimal information to establish eligibility will be collected from study sites/data sources. Detailed inclusion and exclusion criteria are reported in Table 
1.

**Table 1 T1:** Inclusion and exclusion criteria for the FISH study

**Inclusion criteria**	
	Injury due to motor vehicle crash diagnosed by a medical practitioner, or registered health practitioner, within 28 days of the crash
	Injury due to crash involving a motorised vehicle on land (public/private road/driveway/parking space or private/public land) in NSW
	Injured person is a driver, rider, passenger, pillion passenger, pedestrian (person travelling on foot or operating toy vehicle, pedal car, barrow, billycart, non-motorised wheelchair or skateboard) or cyclist
	Adults aged 17 years or over
	Potential participants from a Non-English Speaking Background (NESB) are included if they are able to answer the interview questions
	Potential participant must be residents of NSW, with a valid Medicare number
**Exclusion criteria**	
	Injury due to crash involving types of land transport other than motorised vehicle such as trains and light rail that are not covered by the CTP
	Dementia or significant pre-existing cognitive impairment affecting ability to consent
	Severe injury, which includes severe traumatic brain injury, spinal cord injury, extensive burns or multiple amputations as these injuries are covered defined by the NSW Lifetime Care and Support Scheme
	Isolated, superficial soft tissue injuries such as bruises, abrasions or cuts were also excluded as these very minor injuries are not covered by the CTP
	Injury occurring as a result of intentional self-harm
	Death of an immediate family member in the motor vehicle crash

### Participant identification and sampling

Participants will be recruited from the following sites:

*Hospital Emergency Departments:* Data will be collected at two major Sydney metropolitan region hospitals (Royal Prince Alfred and Royal North Shore) recruiting 600 participants from each hospital. In addition, approximately 400 participants will be identified from three emergency departments in rural NSW (Orange, Dubbo and Bathurst Health Services). Research nurses at each site will screen the “First Net” emergency department data base to identify potential participants.

*General practitioners:* We aim to recruit 200 participants through General Practitioners at two urban primary healthcare networks: the North Shore Medicare Local and Inner West Medicare Local. Medicare Local services are geographically-defined organisations that coordinate the provision of community based healthcare in their region. General practitioners will be reimbursed for their time for assisting in identifying participants for the study.

*Physiotherapists:*Twenty physiotherapy practices will be approached by study staff in the Sydney region to identify potential participants for the study. Recruitment of approximately 200 participants is planned from physiotherapy practices. Physiotherapists will be reimbursed for their time for assisting in identifying participants for the study.

The screening data from study sites will be entered on a secure online platform, Research electronic data capture (REDCap)
[5].

*Police Crash Data source:* Police data will be accessed to identify 150 participants with non-catastrophic injury from rural New South Wales.

*NSW Motor Accidents Authority Registry:* Approximately 200 potential participants will be identified on a monthly basis from the Claims Advisory database and Personal Injury Registry. These are claims databases maintained by the government motor accident insurance regulator.

### Recruitment and consent

From the study sites, data for potential participants based on eligibility criteria will be entered on a secure online platform, Research electronic data capture (REDCap)
[5]. Once screened, potential participants will be sent a letter which details the purpose of the study, what is involved and inviting them to participate in the study. Participants can opt-out of the study via phone or through email. Participants who do not opt-out, within one-week of the letter mail-out, will be contacted by trained interviewers. Interviewers obtain informed consent by telephone and conduct the baseline structured interview. Participants will be asked to consent to their data being accessed from Medicare (the Australian universal health insurance scheme) and from the Pharmaceutical Benefit Scheme, and to being contacted for future follow-up interviews
[22]. The interviews will be conducted using Computer Aided Telephone Interview (CATI) by trained interviewers. Follow-up interviews will be conducted by telephone or through e-mail at 6, 12 and 24 months. It is anticipated that 70 to 85% of the cohort will be retained at 24 months
[10].

Health and social recovery outcome data and variables that potentially influence these outcomes will be collected though a telephone interview using multiple standardised measures, as reported in Table 
2. The focus is on key variables known to be associated with health outcomes. The duration of baseline telephone interview will be no longer than 45 minutes and follow –up interviews will be of approximately 10–15 minutes.

**Table 2 T2:** Data collected at baseline and follow-up for the FISH study

**Baseline**	
Socio-demographic	Age, sex, place of birth, primary language, education, marital status
Employment	Employment status, occupation, income
Health	BMI ( height and weight), history of chronic illness
Health related quality of life	Likert scale for overall health, EQ5D3L [23] and SF12 [24] prior to crash and at baseline, Global Perceived Effect (GPE) [25].
Lifestyle habits	Smoking status and alcohol consumption
Pain	Numeric Rating Scale (NRS) [26], Pain Catastrophising Scale (PCS) [27], Orebro Musculoskeletal Pain Question (OMPQ, short form) [27].
Disability and functioning	History of any disability, World Health Organisation Disability Assessment Schedule II (12-item version) (WHODAS II) [28].
Psychological factors	Perceived threat to life and disability, Depression, Anxiety and Stress Scale (DASS21) [29] and Impact of Events Scale (IES-R) [30], expectation to recover using OMPQ.
Health Care Utilisation	Visit to health care professionals 3 months prior to crash, history of health care utilization in 12 months prior to crash through Medicare data linkage
Injury	Type of injury and associated hospitalisation
Crash related factors	Role, perceived danger of death and disability
Work	Return to work, modified duties, hours
Social life	Satisfaction with social relationships

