### Baseline and follow-up data and study endpoints

Data from multiple domains will be recorded at baseline and the follow-up interviews as reported in Table 
2. Standardised instruments are used that assess the relevant domains based on previous research.

The primary outcomes are health related quality of life, disability and functioning at 6, 12 and 24 months after injury in motor vehicle crash. The secondary outcomes are pain status, psychological health, return and modification to work status, social outcomes, role of compensation and health care utilisation.

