### Data linkage

Pre-injury health status is recognised as a confounder in studies of health outcomes after motor vehicle crashes. It can be measured by recall from the injured person but this may be biased. To avoid this, participant consent will be obtained to access Medicare records for the 12 month period prior to the crash date and for two years after the crash. These data will be linked with the data collected directly from participants. The details of variables that will be collected from Medicare records are listed in Table 
3. Previously a systematic review has reported consent rate to range between 39%-97% for data linkage
[20]. It was observed that in general, individuals tend to consent to the use of their data for record linkage, with exceptions in specific populations or minorities. We anticipate a consent rate of approximately 80% for the study.

**Table 3 T3:** Data collected through Medicare and Pharmaceutical Benefit scheme

**Variables from medicare data**	**Description**
Date of service	Date on which the provider performed the service
Date of processing	Date on which Medicare processed the payment of a claim for the service
Medicare benefits Item description	Describes the service provided by the provider as per Medicare Benefits Schedule
Medicare item number	A number that identifies the service provided by the provider as per Medicare Benefits Schedule
Provider charge	The amount the provider charged for the service
Schedule fee	The fee listed in the Medicare Benefits Schedule
Benefit paid	The Medicare benefit paid to the claimant
Patient out of pocket	The amount the patient is out of pocket i.e. provider charge minus benefit paid Bill
Type	Method by which the Medicare benefit was claimed i.e. cash, bulk bill, cheque to claimant, cheque to provider via claimant, PCE (Easy claim patient claim), simplified bill and EFT
Scrambled ordering provider number	A scrambled provider number identifying the doctor who referred the service scrambled
Rendering provider number	A scrambled provider number identifying the doctor who provided the service
Date of referral	The date of referral or request for a service by a provider
Rendering provider postcode	Postcode of servicing provider’s practice location
Ordering provider postcode	Postcode of referring provider's practice location
Hospital indicator	An indicator of whether the service was performed in hospital
Provider speciality	Speciality of the provider as at time of service

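### WHODAS II, the only listed scale for the primary disability domain, has no pre-crash rating, so change from pre-injury disability cannot be estimated and adjustment rests on proxies

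*Protocol article*

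**What the plan says.** The section on baseline and follow-up data and study endpoints states: "The primary outcomes are health related quality of life, disability and functioning at 6, 12 and 24 months after injury". Quality of life and disability are thus both primary domains.

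The baseline block of Table 2 treats them differently. The quality-of-life row reads "Likert scale for overall health, EQ5D3L [23] and SF12 [24] prior to crash and at baseline". The disability row reads "History of any disability, World Health Organisation Disability Assessment Schedule II (12-item version) (WHODAS II", with no pre-crash label. In the follow-up block WHODAS II is again the only standardised scale in the disability row.

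The timing is given in the Abstract: "Baseline interviews will be conducted by telephone within 28 days of the injury". The first WHODAS II score is therefore always a post-crash score.

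The Data linkage section says: "Pre-injury health status is recognised as a confounder in studies of health outcomes after motor vehicle crashes". It warns that recall of pre-injury health may be biased and turns to linkage: "participant consent will be obtained to access Medicare records for the 12 month period prior to the crash date". About 80% are expected to consent. The Data analysis section plans mixed models adjusted for potential confounders.

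**The concern.** A participant who was disabled before the crash and returns fully to that level has a poor WHODAS II score at 6, 12 and 24 months. On that scale alone, this person looks the same as someone left disabled by the crash. For quality of life the plan holds a score that tells the two apart; for disability it does not.

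Two groups of hypotheses in the Discussion are exposed.

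- **Pre-injury factors.** Poor pre-injury health is expected to go with worse outcomes. Part of any such association with WHODAS II may be earlier disability measured again.
- **Compensation factors.** Claim-process factors are to be assessed with adjustment for disability, among other things. The only scaled early disability score on the outcome's own instrument is the post-crash one, which mixes earlier and injury-related disability.

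The random effect for participant in the planned models does not solve this. It allows for correlation between repeated scores, but it does not remove confounding of a between-person predictor by a stable pre-crash level.

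**Working it through.** No stated figure in the protocol depends on this point, so there is none to reproduce. The check is a comparison of the measures, followed by an illustration of size.

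**Step 1. What is known about the pre-crash state (Table 2; Data linkage; Table 3)**

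| Source | Pre-crash state covered? | Limits as an adjuster for WHODAS II |
|---|---|---|
| WHODAS II, 12 items | No | First score is post-crash, within 28 days |
| SF12, EQ5D3L | Yes, recalled | Scored, but different instruments |
| Disability history | Yes | Not listed as a scaled score; response format not given |
| Chronic illness ("history of chronic illness") | Yes | Illness, not functioning |
| Health-care visits, 3 months before the crash | Yes, recalled | Service use, not functioning |
| Medicare and PBS records | Yes, Medicare for 12 months before the crash | Services, costs and prescriptions; about 80% consent |

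At 80% consent, 2400 × 0.80 = 1920 of the cohort would have linked data and 2400 − 1920 = 480 would not.

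**Step 2. What follows.** Change from pre-injury level needs a pre-crash and a follow-up score on the same scale. The plan lists both for SF12 and EQ5D3L, but only the follow-up score for WHODAS II. The quantity is therefore not estimable for WHODAS II, whatever model is used. Adjustment for earlier disability remains possible, but only through the proxies above.

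**Step 3. How much confounding a proxy leaves (illustration).** These assumptions are not in the documents:
- all variables are standardised;
- the predictor X has no true effect;
- X correlates ρ = 0.2 to 0.4 with pre-crash disability D;
- D correlates b = 0.4 to 0.6 with follow-up WHODAS II;
- the proxy P, or the best combination of proxies, correlates r with D and is related to X and to the outcome only through D.

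Unadjusted coefficient of X: bρ.

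Coefficient of X adjusted for P: (bρ − br·ρr) / (1 − ρ²r²).

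Share of bias left, the second divided by the first: (1 − r²) / (1 − ρ²r²). This does not depend on b.

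Example with r = 0.7: (1 − 0.49) / (1 − 0.04 × 0.49) = 0.51 / 0.9804 = 0.52 for ρ = 0.2, and 0.51 / (1 − 0.16 × 0.49) = 0.51 / 0.9216 = 0.55 for ρ = 0.4.

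| r | Share of bias left, ρ = 0.2 to 0.4 |
|---|---|
| 0 | 100% |
| 0.5 | 76 to 78% |
| 0.7 | 52 to 55% |
| 0.8 | 37 to 40% |
| 0.9 | 20 to 22% |
| 1 | 0% |

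The documents do not give r, so the table shows only how the answer depends on it.

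**The case against.** The strongest reply has four parts.

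- **The plan does hold pre-crash information.** Disability history, chronic illness, scored pre-crash SF12 and EQ5D3L, and linkage are all available, and confounder adjustment is planned. This stands. A reader might infer from the missing score that earlier and injury-related disability cannot be told apart at all. The documents do not support that: the proxies allow partial separation, and the SF12 and EQ5D3L scores do not depend on linkage consent.
- **The first objective is prognostic.** Outcomes are defined as status at three time points, and persisting earlier disability is a real predictor of later status. This also stands. It would be wrong to say that the hypothesis on pre-injury health is bound to be confirmed. The concern applies where the result is read as recovery from the injury or as an effect of compensation.
- **A pre-crash WHODAS II would itself be recalled**, and the Data linkage section distrusts recall. This stands as a downside but does not decide the matter. The plan already accepts recalled pre-crash scores for its other primary domain, and linkage, its remedy, does not record functioning.
- **An article condenses the questionnaire.** This is a fair caution. But Table 2 itself marks which scales are rated for the pre-crash state, and WHODAS II is not among them.

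A reader might also infer that the baseline WHODAS II asks about days before the crash. The article states no recall period, so whether there is any overlap cannot be established from it.

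**Conclusion.** The point holds in a limited form. As listed in Table 2, one primary domain has a pre-crash rating and the other does not. Change from pre-injury level is not estimable on WHODAS II, and adjustment for earlier disability relies on proxies, so residual confounding is possible in the analyses of pre-injury and compensation factors.

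The size is unknown. It depends on how closely the proxies together track pre-crash disability; under the assumptions stated, anything from about three quarters of the bias (r = 0.5) to about one fifth (r = 0.9) would remain. The conclusion about estimability needs none of those assumptions. It rests only on Table 2 being a complete list of what is asked.

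This is a cheap and worthwhile improvement in measurement. It does not invalidate the design.

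**What to change.** 1. In the baseline interview, also ask the 12 WHODAS II items for the period before the crash, as is already done for EQ5D3L and SF12. Adjust the WHODAS II outcome models for that score.
2. Where that score is missing, or was not collected, adjust the WHODAS II models for pre-crash SF12, pre-crash EQ5D3L and disability history. In that case, say that change from pre-injury level is not estimated for this outcome.
3. Wherever a post-crash baseline score enters a model, include days from crash to interview as a covariate. Both dates are already known.

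**Cost.** Item 1 adds 12 questions, probably a few minutes, which must fit within the 45-minute limit in the Recruitment and consent section; the article gives no item count from which to work this out exactly. The new score is recalled and may be biased, so it should reduce residual confounding but will not remove it. Items 2 and 3 need no new data.
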